## Abstract

**Background:**

The incidence of postoperative nausea and vomiting (PONV) is 50 to 79% after neurosurgery. Our study is designed to evaluate the efficacy of pericardium 6 (P6; also known as Neiguan) acupoint stimulation versus placebo, and versus routine antiemetic for the prevention of PONV after craniotomy, as well as to compare the efficacy of invasive acupuncture with non-invasive transcutaneous electrical nerve stimulation (TENS) on P6.

**Methods/design:**

This is a single-center, prospective, double-blind, five-arm, parallel-group, randomized controlled trial (RCT). All groups will be given routine intravenous ondansetron 8 mg administered before skin closure. Upon regaining consciousness from general anaesthesia, patients will receive one of five interventions: 1) P6 acupuncture bilaterally for 30 minutes, stimulated every 10 minutes to keep *de qi* sensation; 2) sham acupuncture bilaterally for 30 minutes with no stimulation; 3) P6 stimulation via active TENS electrodes bilaterally for 30 minutes, with stimulation frequency and intensity set to when *de qi* sensation is felt; 4) sham P6 stimulation via inactive TENS electrode bilaterally for 30 minutes; and 5) usual practice of pharmacological emesis prevention. The incidence of postoperative vomiting during the first 24 hours is the main outcome. Secondary outcomes include: complete response rate, severity of nausea, total rescue metoclopramide dose used and patient satisfaction with PONV management.

**Discussion:**

The results from this study could potentially confirm that P6 acupoint stimulation is an effective adjunct to standard antiemetic drug therapy for the prevention of PONV in patients undergoing craniotomy. Our study may also confirm that conventional acupuncture is more effective than TENS.

**Trial registration:**

This study is registered with the Chinese Clinical Trial Registry: ChiCTR-TRC-13003026.

## Background

As a common complication of anesthesia and surgery, postoperative nausea and vomiting (PONV) remains problematic despite use of antiemetics. PONV delays the patient’s recovery from anesthesia, extends their hospital stay and increases overall healthcare costs [1]. Although PONV is rarely fatal, the physical act of vomiting may increase cerebral intravascular pressure or intracranial pressure, which may lead to cause severe consequences in patients who have undergone craniotomy. Studies have reported an average incidence of PONV of up to 38.3% following common surgeries [2], while in patients specifically undergoing neurosurgery, the incidence is as great as 50 to 79% [3,4]. There are no significant differences in the frequency of nausea based on the craniotomy location [5]. PONV has a multi-factor etiology and the mechanism is complex. Currently, pharmacological prophylaxis is widely used in clinical practice, and the most commonly used prophylactic antiemetics include serotonin (5-HT_3_) receptor antagonists often in combination with either droperidol or dexamethasone [6,7]. Although droperidol is very effective, it can cause death secondary to arrhythmia or QT prolongation [8]. At present, no therapy is absolutely effective at preventing PONV.

Due to the limited efficacy and many side effects of drug therapy, various non-pharmacological techniques have been used in clinical practice. These therapies include acupuncture, acupressure, transcutaneous electrical nerve stimulation (TENS), electro-acupuncture, and others. Early in 2006, the American Society of PeriAnesthesia Nurses (ASPAN) recommended pericardium 6 (P6; also known as Neiguan) acupoint stimulation (Class IIb, Level A) as a complementary intervention for PONV prophylaxis [9]. According to the theory of traditional Chinese medicine (TCM), performing surgery breaks the balanced state of the human body and disturbs the movement of both *qi* and blood. When this happens, stomach *qi* will reverse its direction and go upward, causing nausea and vomiting. The main principle of treatment in this case is to regulate the function of the stomach to avoid the adverse flow of *qi*. P6 is an acupuncture point in the meridian named Jueyin Pericardium Meridian of Hand. It is both the Luo-connecting point (the point where a collateral starts to connect a definite pair of Yin and Yang meridians, which are externally-internally related) and the eight confluent point (the point connecting the eight extra meridians with the twelve primary meridians). One of P6’s main functions is to regulate the function of the stomach to avoid the adverse flow of *qi*, thus it is an effective acupoint for preventing nausea and vomiting.

Many recent studies have supported the efficacy of P6 acupoint stimulation for preventing PONV [10-12], with very few gaining a negative result [13,14]. The various ways to stimulate the P6 acupoint include laser, electrical, transcutaneous electrical and manual stimulation. Few studies have compared the efficacy of invasive methods with non-invasive methods. Thus, the optimal method of stimulation has not been determined due to lack of evidence. Although there is a great amount of research concerning P6 acupoint stimulation for preventing PONV, only two studies focus on the role of P6 acupoint stimulation in postoperative patients following craniotomy [15,16]. Therefore, we designed a single-center, prospective, double-blind, five-arm, parallel-group, randomized controlled trial (RCT) to evaluate the efficacy of P6 acupoint stimulation as a non-pharmacological prophylaxis for PONV.

The primary objective of this study is to evaluate the efficacy of P6 acupoint stimulation versus placebo, and versus routine antiemetic for the prevention of PONV in patients undergoing craniotomy under general anesthesia. The secondary study objective is to compare the efficacy of invasive acupuncture with non-invasive TENS on P6. We hypothesize that a significantly greater percentage of patients will not vomit in the subsequent 24 hours following craniotomy in the acupoint stimulation groups. Additionally, we expect that the severity of nausea will be decreased in the acustimulation groups, based on subjective patient feedback.

## Methods/design

### Design

This is a single-center, prospective, double-blind, five-arm, parallel-group, RCT. The trial protocol strictly follows the principles of the Declaration of Helsinki (version Seoul, 2008) and approval has been obtained from Si-chuan University's Ethics and Research Committee. Participants have been and will continue to be recruited from the West China Hospital of Si-chuan University (WCHSU) from January 2013 to October 2013 (Figure 1). All participants are required to give written informed consent.

**Figure 1 F1:**
[figure not shown]
**Trial flow chart.** If a patient can not complete the study due to death, re-operation, unconsciousness or cognitive impairment, the patient will be considered a lost case and recorded as an occurrence of PONV. PONV, postoperative nausea and vomiting; TENS, transcutaneous electrical nerve stimulation.

### Patient population and setting

A total of 300 Chinese patients undergoing craniotomy will be sequentially recruited at the WCHSU after fulfilling the eligibility criteria and signing the informed consent. A clinical assistant with institutional review board training will be in charge of patient enrollment.

### Eligibility criteria

#### Inclusion criteria

Patients who fulfill the following conditions will be included: 1) scheduled for neurosurgery requiring opening of the cranium and dura; 2) aged between 18 and 70 years old; 3) American Society of Anesthesiologists (ASA) physical status classification of I or II; 4) undergoing general anesthesia; 5) no history of PONV or motion sickness; 6) no use of antiemetic 24 hours before surgery; 7) willing to participate; 8) no experience with acupuncture therapies; and 9) signed an informed consent form.

#### Exclusion criteria

Participants that meet any of the following criteria will be excluded: 1) nausea or vomiting 24 hours before surgery; 2) pregnant or lactating women; 3) drug or alcohol abusers; 4) recipients of chemotherapy or radiation therapy during the previous 7 days; 5) cardiac pacemaker; 6) menstruating phase of the menstrual cycle; 7) refusal to accept acupuncture and TENS treatment; 8) mental disorder; 9) history of epilepsy and still taking an antiepileptic medicine; 10) unconscious before the surgery; 11) cannot normally communicate; 12) undergoing ventricle or brainstem surgery; 13) cerebral perfusion pressure (CPP) of less than 50 mmHg or greater than 150 mmHg; 14) poorly controlled diabetes mellitus (fasting plasma glucose greater than 12 mmol/L); 15) bleeding disorders (hemophilia or afibrinogenemia); and 16) serious systemic disease (AIDS or sepsis).

### Randomization and blinding

The randomization sequence will be computer-generated by independent research staff using software called Package for Encyclopaedia Medical Statistics 3.1 (PEMS 3.1). Stratification will not be used in this trial. After randomization, group assignments will be concealed in light-proof and sealed envelopes. The included participants will be randomly enrolled by sealed envelope and assigned to the acupuncture group, sham-acupuncture control group, TENS group, placebo-TENS control group and usual treatment group, using a 1:1:1:1:1 ratio. Patient allocation will be performed by a clinical assistant, who will be trained in institutional review board policies. All study personnel including the outcome assessors, study participants, data analyst and care providers will be blinded to group assignments.

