When the patients regain consciousness from anesthesia and are able to communicate, the intervention will begin. All participants in our study will receive the intervention only once. In preparation for acustimulation, the patient will be placed in the best posture for P6 acupuncture, with their forearms fully exposed and with their palms facing upward. A fourth-year acupuncture resident will locate the P6 acupoint bilaterally (Figure 2) and perform the interventions specified in Table 1. P6 is an important acupuncture point in the Jueyin Pericardium Meridian of Hand. The location of P6 is 2 cun (a cun is a measurement used in acupuncture and is equivalent to the width of the distal interphalangeal joint of the first finger) above the transverse crease of the wrist, between the tendons of palmaris longus and flexor carpi radialis.

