**Figure 2 F2:**
[figure not shown]
Location of P6 acupoint and sham acupoint.

**Table 1 T1:** Details of interventions

**Group names**	**Acupoints**	***De qi *****sensation**	**Interventions**
Acupuncture group	P6 (Neiguan) bilaterally	Yes	P6 at both sides is punctured perpendicularly to a depth of 20 mm. Needles are retained for 30 minutes and stimulated every 10 minutes to keep the *de qi* sensation.
(group A)			
Sham-acupuncture control group	Sham points bilaterally	No	The sham point is punctured to a perpendicular depth of 5 mm bilaterally. Needles are retained for 30 minutes and no stimulation is performed during this duration.
(group SA)			
TENS group	P6 (Neiguan) bilaterally	Yes	P6 acupoint at both sides is stimulated by active self-adhesive electrodes for 30 minutes. The stimulation frequency is set on 2 to 100 hertz and intensity varies until the patients continue to feel the *de qi* sensation.
(group T)			
Placebo-TENS control group	P6 (Neiguan) bilaterally	No	Inactive self-adhesive electrodes are placed at the P6 acupoint bilaterally for 30 minutes.
(group PT)			
Usual treatment group	—	—	—
(group U)			

TENS, transcutaneous electrical nerve stimulation.

For the acupuncture group (group A), after skin cleaning with 75% alcohol swab, sterile and disposable stainless steel needles (0.25 × 25 mm, Wuxi Jiajian, Jiangsu, China) are quickly and perpendicularly inserted into the skin at P6 acupoints bilaterally to a depth of 20 mm. In this group, downward pressure and upward lifting combined with twirling the needle will be used to achieve *de qi* sensation. The needles will be kept in place for 30 minutes and manipulated manually every 10 minutes to maintain the *de qi* sensation. When the treatment time is over, all needles will be carefully taken out and the puncture sites will be covered with sterile swabs to avoid bleeding.

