**Figure 3 F3:**
[figure not shown]
The SDZ-V nerve and muscle stimulator (Hwato, Jiangsu, China) and self-adhesive electrodes.

For the placebo-TENS control group (group PT), patients have self-adhesive electrodes placed over P6 acupoints bilaterally, and are connected to the SDZ-V nerve and muscle stimulators for 30 minutes. However, as a placebo control group, the stimulators will not be turned on and there will be no electrical stimulation during the treatment. In order to blind patients in this group, each participant will be informed that special acupoint stimulation is used in the treatment which cannot be felt by human sensory perception. After 30 minutes, all self-adhesive electrodes will be removed as in the group T.

For the usual treatment group (group U), no interventions are undertaken. Patients in this group will be observed by the researchers as a blank control, which will provide a baseline postoperative vomiting rate and nausea score in this study using the same drug prophylaxis.

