### Outcome measurement

In our study, outcomes are collected based on previously designed PONV studies [18]. The whole study period covers 24 hours after the surgery. A separate research nurse, who is not involved in the management of patients, will record anesthesia time, surgery time, endotracheal intubation time, patient demographics and preoperative data for each patient. Demographic and preoperative data will include: age, gender, race, weight, height, acupuncture experience, smoking history and CPP. Another blinded observer will record the postoperative data, which will include administration of a rescue antiemetic, patient satisfaction with PONV management, and episodes of vomiting or nausea at 2 hours, 6 hours and 24 hours postoperatively. The physicians will record the use time and dosage of rescue antiemetic for each patient when they request rescue therapy, and the records will be handed over to the observer for assessment. Nausea is a subjective sensation which should be evaluated by the patient, not by the observer. Thus, the observer will request the patients to evaluate their nausea score using a standard visual analogue scale (VAS) (0, no nausea at all; 10, worst imaginable nausea). Vomiting, which is defined as the ejection of contents of the stomach through the mouth, will be reported by the patients and assessed by this blinded observer. Patient satisfaction is not an easy concept to measure. Until recently, there has been no consensus on how to measure this concept. Since satisfaction is multi-faceted and subjective, a questionnaire cannot cover every aspect of a patient’s concerns. Therefore, in this study, patients will be asked about satisfaction with their PONV treatment at 24 hours postoperatively using another 0 (very dissatisfied) to 10 (very satisfied) scale.

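### The blanket blinding statement cannot hold: group U patients, the treating resident and the needle-versus-electrode comparison are not blinded, so the routine-antiemetic part of the primary objective is open to patient and provider

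*Protocol article*

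**What the plan says.** Under Randomization and blinding, the protocol article states: "All study personnel including the outcome assessors, study participants, data analyst and care providers will be blinded to group assignments". Under Design it states: "This is a single-center, prospective, double-blind, five-arm, parallel-group, RCT". Neither sentence is limited to particular arms or contrasts.

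The Interventions section describes what is done:

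- Timing: "When the patients regain consciousness from anesthesia and are able to communicate, the intervention will begin".
- Provider: "A fourth-year acupuncture resident will locate the P6 acupoint bilaterally". The same resident then performs the procedures listed in Table 1.
- Fifth arm: "For the usual treatment group (group U), no interventions are undertaken", and "Patients in this group will be observed by the researchers as a blank control".

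Under Outcome measurement, vomiting "will be reported by the patients and assessed by this blinded observer". Nausea and satisfaction are rated by the patient on 0 to 10 scales. The Interventions section has rescue antiemetic given when the patient asks for it.

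The primary objective, at the end of the Background, has two parts: P6 stimulation against placebo, and against routine antiemetic. Acupuncture against TENS is the secondary objective.

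**The concern.** The blinding sentence asserts a property that some of the comparisons cannot have. A reader of the eventual report would take every contrast in a trial labelled double-blind as protected from expectation. The contrast with routine antiemetic matters most, because it is part of the primary objective and its control arm has nothing that imitates the treatment. The outcomes rest largely on what patients report or request. A lower event rate in A or T than in U could therefore partly reflect knowing that something extra was given, yet be presented as blinded evidence that P6 stimulation works.

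**Working it through.** **Who can be blinded, by contrast.** These points come from the Interventions section, Table 1, Outcome measurement, and Sample size calculation and statistical analysis.

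- Group U patients are conscious during the period when other patients have needles or electrodes on both forearms for 30 minutes. Nothing is applied to them. Refusal of acupuncture and TENS is an exclusion criterion, which implies that candidates have been told of both. The cover story that the stimulation cannot be felt does not help, because group U has no electrodes.
- The resident needles P6 to 20 mm and manipulates to a sensation (A), or needles an off-point to 5 mm without manipulation (SA). For the electrode arms, intensity is varied until the patient feels the sensation (T), or the stimulator is not turned on (PT). Tape over the screen does not hide these tasks from the person performing them.
- An awake patient can tell needles from electrodes.

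| Contrast | Objective | Patient | Resident | Observer and statistician |
|---|---|---|---|---|
| A vs SA | Primary, versus placebo | Masked to active or sham, by design | Not blinded | Intended blinded |
| T vs PT | Primary, versus placebo | Masked to active or sham, by design | Not blinded | Intended blinded |
| A vs U, T vs U | Primary, versus routine antiemetic | Not blinded | Not blinded | Intended blinded |
| A vs T | Secondary | Knows the modality | Not blinded | Intended blinded |

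All five arms receive ondansetron, and only U receives it with no procedure. The routine-antiemetic question therefore has no other comparator.

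**The plan's own figure.** Inputs from the sample size section: 47% reduced by 30 points to 17%, two-sided α = 0.05, 90% power.

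n = [1.960·√(2·p̄(1−p̄)) + 1.282·√(p₁(1−p₁)+p₂(1−p₂))]² / (p₁−p₂)², with p̄ = 0.32

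= [1.960·√0.4352 + 1.282·√0.3902]² / 0.09 ≈ 48.7, so 49 per group.

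This reproduces the stated 49. The planned 60 allows for 1 − 49/60 = 18% attrition. The blinding point does not change this calculation.

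**Illustration of what expectation could do.** The documents give no size for such an effect, so b below is an assumption. Take 47% in U, 47% − b in the active arm with no true effect, and 60 per arm. The chance of unadjusted two-sided P<0.05 in favour of the active arm is

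Φ{ [b − 1.960·√(2p̄(1−p̄)/60)] / √([p₁(1−p₁)+p₂(1−p₂)]/60) }.

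- b = 0.05: (0.050 − 0.1778)/0.0906 = −1.41, giving 7.9%.
- b = 0.10: (0.100 − 0.1766)/0.0896 = −0.85, giving 19.6%.
- b = 0.15: (0.150 − 0.1749)/0.0882 = −0.28, giving 38.9%.

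With b = 0 the nominal rate in that direction is 2.5%.

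**The case against.** Much of the design is sound, and the article does not hide the difficulty. Each modality has its own sham, the stimulator screens are taped, and patients must have no experience of acupuncture. The Discussion names patient blinding as the hardest part. Group U is openly described as a blank control, not a placebo. A separate blinded observer records postoperative data, and a blinded statistician works at another site. Vomiting is a discrete physical event and less open to expectation than a nausea scale. All of this stands. It supports the two sham contrasts, but it supplies no masking for group U patients. An observer also cannot remove bias already present in a patient's report.

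It may be said that care providers means ward and recovery staff. The sentence begins with all study personnel, however, and the resident is one of them.

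The illustration is also open to challenge. The 47% is an incidence of nausea and vomiting combined, whereas the main outcome is vomiting. The plan names multiple-comparison procedures, which the unadjusted figures ignore. Even at 15 points the test is non-significant about 61% of the time. These are fair limits: the figures show what could happen and do not estimate what will.

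A reader might infer from the article that the observer is unblinded too, because in the acupuncture group "the puncture sites will be covered with sterile swabs to avoid bleeding" and the sham group's needles are removed in the same way. The documents do not support that. They do not say that swabs remain at the 2-hour visit or that the observer looks at the forearms, and such a clue would reveal the modality, not active versus sham.

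**Conclusion.** The blinding sentence and the unqualified double-blind label are wrong as written. The error covers group U patients, the resident, and patients' awareness of modality in the secondary comparison. The consequence for the primary objective comes from group U alone: the part against routine antiemetic is unblinded to patient and provider. It would go too far to call that part open-label without qualification, because blinded outcome recording and analysis are planned and nothing shows that either fails. It would also go too far to count needle against electrode as a primary-objective problem, since that comparison is secondary.

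On the size, an expectation effect could contribute to a difference from U. The rates of about 8%, 20% and 39% rest on assumed reporting differences of 5, 10 and 15 points, a 47% rate in U, 60 analysed per arm and no multiplicity adjustment. The conclusion that the statement is wrong does not depend on these figures. The placebo part of the primary objective keeps its patient masking and its intended observer blinding, but not provider blinding.

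**What to change.** Replace the blanket sentence with a statement by contrast:

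- patients are blinded to active versus sham within a modality only (A vs SA, T vs PT);
- patients are not blinded to modality, and group U patients are not blinded;
- the acupuncture resident is not blinded;
- the observer and the statistician are intended to be blinded.

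Qualify the double-blind label to match, in the Abstract, Background and Design. State that any claim of a P6-specific effect will rest on A vs SA and T vs PT. Report A vs U and T vs U as the effect of the whole package of care, not blinded to patient or provider. Note that A vs T is not blind to modality.

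The cost is a change of wording and a less favourable design label. Procedures, sample size and data collection are unchanged, so it can be made while the trial is recruiting.

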### Interventions

In this trial, we will use both invasive and non-invasive methods to stimulate the P6 acupoint as an adjunct to routine antiemetic drug therapy for the prevention of nausea and vomiting in patients undergoing craniotomy. The routine antiemetic treatment for high-risk patients at the WCHSU is a single intravenous dose of 8 mg ondansetron administered before skin closure. Therefore, neither dexamethasone nor droperidol will be used in our study.

To date, the optimal timing of acustimulation for preventing PONV has not been determined. In our study, the intervention is started right after the patient regains consciousness from anesthesia for two reasons. First, in the TCM theory, it is important to locate the right acupoint with the *de qi* sensation (the sensation of numbness, heaviness or distention associated with correct identification of an acupuncture point) to enhance efficacy, and this cannot be accomplished when the patient is unconscious. Second, a recent RCT shows that postoperative acustimulation is more effective in reducing PONV [17].

In preparation for surgery, all patients will receive a standard anesthesia and analgesia regimen specific to neurosurgical procedures. They will fast for 8 hours before general anesthesia. Standard monitors will be used to record patients' electrocardiogram, pulse oximetry, invasive arterial blood pressure and end tidal CO_2_. Induction of anesthesia will be achieved with midazolam 0.05 mg/kg, sufentanil 0.3 μg/kg, atracurium 0.15 mg/kg and propofol 2 mg/kg. When endotracheal intubation and gastrointestinal decompression with either an orogastric or nasogastric tube are undertaken, the anesthesia will be maintained with 50% nitrous oxide and 3% sevoflurane, and intermittent sufentanil 0.2 μg/kg and atracurium 0.1 mg/kg. Intravenous ondansetron 8 mg is administered as a routine antiemetic treatment for each patient before skin closure. Fentanyl 25 to 50 μg intravenous boluses are used as needed for postoperative, patient-controlled intravenous analgesia (PCIA). After surgery, patients will be continually monitored in the post-anesthesia care unit (PACU). Tracheal extubation will be undertaken when patients regain consciousness from anesthesia. Intramuscular metoclopramide 10 mg will be used as a standard rescue antiemetic and administered at the patient’s request.

When the patients regain consciousness from anesthesia and are able to communicate, the intervention will begin. All participants in our study will receive the intervention only once. In preparation for acustimulation, the patient will be placed in the best posture for P6 acupuncture, with their forearms fully exposed and with their palms facing upward. A fourth-year acupuncture resident will locate the P6 acupoint bilaterally (Figure 2) and perform the interventions specified in Table 1. P6 is an important acupuncture point in the Jueyin Pericardium Meridian of Hand. The location of P6 is 2 cun (a cun is a measurement used in acupuncture and is equivalent to the width of the distal interphalangeal joint of the first finger) above the transverse crease of the wrist, between the tendons of palmaris longus and flexor carpi radialis.

